## Abstract

**Introduction:**

Fu’s Subcutaneous Needling (FSN) is a novel acupuncture technique that has demonstrated significant efficacy in pain management. However, its effectiveness in treating migraine without aura (MWoA) has not been systematically validated. Therefore, this study aims to evaluate the analgesic efficacy of FSN and its impact on headache frequency and patients’ quality of life (QoL) in comparison with guideline-recommended pharmacotherapy (flunarizine hydrochloride). Additionally, this study will assess the influence of FSN on hemodynamic changes in the prefrontal cortex to further elucidate its underlying mechanisms.

**Methods:**

This study is a randomized controlled clinical trial involving 44 participants, who are randomly allocated at a 1:1 ratio to either the FSN group or the medication group. Participants in the FSN group receive FSN treatment twice weekly for 4 weeks, while those in the medication group are administered 5 mg oral flunarizine hydrochloride capsules nightly for the same duration. Both groups are followed up for 3 months post-treatment. The primary outcome is the change in monthly migraine days (MMDs). From baseline after 4 weeks of treatment. Secondary outcome measures including the Migraine-Specific Quality of Life (MSQOL) score, headache diary records, Migraine Disability Assessment (MIDAS), Visual Analog Scale (VAS) scores and near-infrared spectroscopy (NIRS) are also used to validate clinical efficacy.

## Introduction

1

Migraine is a primary headache disorder marked by recurrent episodes of moderate to severe throbbing pain, often accompanied by symptoms such as nausea, vomiting, photophobia, or phonophobia (1). It adversely affects patients’ daily activities and quality of life to varying degrees (2, 3). According to the 2015 Global Burden of Diseases (GBD) study, migraine ranks as the second most prevalent neurological disorder associated with disability (38). Epidemiological surveys indicate that the annual prevalence of migraine in China is 9.3%,with a female-to-male ratio of approximately 2:1 (4). Migraine remains a predominant cause of disability under 50 (5). Currently, the etiology and pathogenesis of migraine remain incompletely understood, and no unified or definitive diagnostic criteria have been established. The primary treatment recommended by clinical guidelines is pharmacotherapy, including preventive medications (e.g., flunarizine hydrochloride) and acute analgesics (e.g., nonsteroidal anti-inflammatory drugs) (1). However, clinical practice often faces challenges such as inadequate preventive treatment and overuse of acute analgesics (6, 7), potentially exacerbating chronic migraine progression or triggering medication-overuse headache (8). Therefore, there is a pressing need to explore safer and more effective non-pharmacological interventions to prevent the onset and progression of migraine.

Emerging evidence indicates that myofascial trigger points (MTrPs) play a significant role in migraine, particularly in migraine without aura (MWoA) (9–11). Compared with non-migraine individuals, MWoA patients exhibit localized tenderness and referred pain in pericranial and cervical muscles that can trigger headaches. The tender points in pericranial muscles are more sensitive even during headache-free periods, and headache intensity correlates positively with tenderness severity. Moreover, the convergence of referred pain from different pericranial muscles can elicit typical unilateral or bilateral migraine-like pain (9–11). The pain sensation elicited by pressing MTrPs in these regions resembles the prodromal symptoms of migraine attacks (12), and the referred pain areas overlap with migraine attack sites (9). Previous studies have applied therapeutic interventions such as acupuncture and repetitive peripheral magnetic stimulation (rPMS) targeting MTrPs in the sternocleidomastoid and trapezius muscles of patients with MWoA. These interventions are found to significantly reduce headache intensity scores and attack frequency post-treatment (13, 14). In summary, MTrPs in migraine patients are predominantly localized in the upper trapezius, sternocleidomastoid, splenius capitis, and suboccipital muscle groups (9, 10, 15–18), which may provide valuable anatomical references for clinical migraine management (see Figures 1–4; Table 1).

**Figure 1 fig1:**
[figure not shown]
Study protocol flowchart.

**Figure 2 fig2:**
[figure not shown]
FSN and insertion device.

**Figure 3 fig3:**
[figure not shown]
Schematic Illustration of FSN Procedure. Using the Trapezius Muscle as an Example: **A–C**: the insertion device is pressed against the skin, then the needle is inserted subcutaneously parallel to the skin surface. **D**: upon completion of needle insertion, the operator performs lateral sweeping motions with the index and ring fingers of one hand while applying resistance with the other hand against the participant, eliciting a shrugging motion with resistance.

**Figure 4 fig4:**
[figure not shown]
Placement of NIRS.

**Table 1 tab1:** Study schedule.

Stage	Baseline	Treatment			Follow-up (after treatment)		
Time point	Day 0	Day 1	→	Day 28	Day 28	→	Day 168
Enrolment							
Eligibility	×						
Informed consent	×						
Allocation	×						
Interventions							
FSN		×					
Flunarizine hydrochloride		×					
Assessment							
MMD	×			×	×	×	×
MSQOL scores	×			×	×	×	×
VAS scores	×			×	×	×	×
MIDAS scores	×			×	×	×	×
Headache diaries	×			×	×	×	×
NIRS		4 measurements					
Adverse events	×	×					

Fu’s Subcutaneous Needling (FSN), developed by [name], is a novel acupuncture technique derived from traditional Chinese medicine and grounded in anatomy, physiology, and myofascial trigger point theory. It involves repetitive sweeping of the subcutaneous loose connective tissue over pathologically tense muscles to reduce peripheral muscle tension (19), combined with resistance exercises to promote tissue reperfusion. This approach rapidly alleviates muscle ischemia and hypoxia (20), reduces mechanical compression on surrounding tissues, and demonstrates notable efficacy in pain management (21, 22).

Currently, there is a paucity of clinical studies on the application of floating acupuncture for MWoA, and objective assessments of its therapeutic effects are lacking. Therefore, we propose a randomized controlled trial to assess the clinical efficacy and underlying mechanisms of FSN in treating MWoA, with the goal of identifying safer and more effective treatment strategies. We hypothesize that floating acupuncture is non-inferior to flunarizine hydrochloride in alleviating pain intensity, reducing attack frequency, and enhancing quality of life in MWoA patients.

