### Sample size calculation

2.4

This study is an exploratory investigation, with the primary outcome measure defined as the reduction in the monthly migraine days (MMD) from baseline after 4 weeks of treatment. As a novel acupuncture technique, Fu’s Subcutaneous Needling (FSN) inevitably lacks high-quality randomized controlled trials (RCTs) to inform sample size estimation. Therefore, reference is made to an internationally rigorous RCT on acupuncture for migraine without aura (23), and the sample size is estimated based on this study, combined with clinical FSN practice and the current study design. The hypothesis posited comparable effect sizes between the two interventions (FSN group and flunarizine hydrochloride group) in this trial and those observed in the prior study’s acupuncture and flunarizine hydrochloride groups. The referenced study reported that after 4 weeks of treatment, the MMD in the acupuncture group decreased by 4.1 ± 3.5 from baseline, while the MMD in the flunarizine hydrochloride group decreased by 1.9 ± 2.3 from baseline. To verify whether the efficacy of FSN is at least not inferior to that of flunarizine hydrochloride, a non-inferiority test is employed. Based on previous research (24), the most commonly selected non-inferiority margin for Monthly Migraine Days (MMD) in migraine studies is 1. The calculation is performed using the Non-Inferiority Tests for the Difference Between Two Means in PASS 15.0 software. With *α* = 0.05 (two-sided), power (1−*β*) = 0.9, and an anticipated 25%dropout rate, a total of 44 participants (22 per group, 1:1 ratio) are required to detect a statistically significant difference in MMD changes between the two groups.

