## Statistical analysis

6

Statistical analyses are conducted using SPSS 25. All tests employ two-sided comparisons, with statistical significance defined as *p* < 0.05.

Normally distributed continuous variables are presented as mean ± standard deviation (SD), whereas non-normally distributed variables are reported as median and inter-quartile range (IQR). Categorical variables appear as frequency and percentage (proportions).

For the MMD, MSQOL, MIDAS and VAS scale scores, between-group differences in changes from baseline to 4 weeks post-treatment are analyzed using either the independent *t*-test or Mann–Whitney U test, as appropriate. Intra-group comparisons between baseline and 4-week post-treatment measurements are conducted using paired *t*-test or Wilcoxon signed-rank test. Given the repeated measurements of MMD and the scale scores, repeated-measures analysis of variance (ANOVA) is additionally employed for supplementary analysis. For near-infrared spectroscopy (NIRS)-derived oxygen saturation levels, analyzed for within-group differences before and after treatment using paired *t*-test.

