## Conclusion

8

The hypothesis of this study is that FSN therapy is not inferior to flunarizine hydrochloride in improving headache intensity and attack frequency in patients with migraine without aura, and that its therapeutic effects may be sustained over time. The study aims to test this hypothesis in a controlled clinical trial. The results may demonstrate the clinical utility of FSN therapy for migraine without aura and facilitate its wider implementation.

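### Non-inferiority is hypothesised for pain intensity and quality of life as well as attack frequency, but only MMD has a margin and VAS and MSQOL get only difference tests

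*Protocol article*

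**What the plan says.** **Hypothesis.** The last paragraph of section 1 (Introduction) hypothesises that FSN is "non-inferior to flunarizine hydrochloride in alleviating pain intensity, reducing attack frequency, and enhancing quality of life in MWoA patients". Section 8 (Conclusion) words it as "FSN therapy is not inferior to flunarizine hydrochloride in improving headache intensity and attack frequency in patients with migraine without aura" and adds that the study aims to test this hypothesis. Quality of life is absent from the second version.

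**Margin and size.** Section 2.4 gives one margin: "the most commonly selected non-inferiority margin for Monthly Migraine Days (MMD) in migraine studies is 1". The sample size of 44 rests on MMD alone.

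**Analysis.** Section 6 makes all tests two-sided with significance at p<0.05, and continues: "For the MMD, MSQOL, MIDAS and VAS scale scores, between-group differences in changes from baseline" to 4 weeks are compared by independent t-test or Mann–Whitney U test. It names no margin and no confidence-interval criterion for any of the four measures.

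**Status of the outcomes.** VAS and MSQOL are secondary (section 4.2). MSQOL is scored separately on three dimensions. Sections 2.4 and 7 call the study exploratory.

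**The concern.** A non-inferiority conclusion needs a margin and a confidence limit that stays inside it. For pain intensity and quality of life the article names the hypothesis and names the test, and the test cannot answer the hypothesis except in one case: a significant advantage for FSN. If FSN does not win on VAS or MSQOL, the planned output is a p-value above 0.05, or one below 0.05 in favour of the drug. Neither supports non-inferiority.

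What is at stake is how the secondary results are read. With 22 or fewer per arm, a real loss of pain relief or quality of life against flunarizine can easily be non-significant. Beside a stated hypothesis of non-inferiority, such a result invites the wrong summary, and a smaller or noisier sample makes it more likely.

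This does not depend on how MMD is handled. If section 6 tested MMD against its 1-day margin, VAS and MSQOL would still have none.

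**Working it through.** **1. What the sample size covers.** Section 2.4 takes two figures from its reference trial: "the MMD in the acupuncture group decreased by 4.1 ± 3.5 from baseline" and "the MMD in the flunarizine hydrochloride group decreased by 1.9 ± 2.3 from baseline". The other inputs are the 1-day margin and α = "0.05 (two-sided), power (1−*β*) = 0.9, and an anticipated 25%dropout rate".

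- Assumed advantage for FSN: 4.1 − 1.9 = 2.2 days. Distance from the margin: 2.2 + 1 = 3.2 days.
- SD: √((3.5² + 2.3²)/2) = √8.77 = 2.96.
- Non-inferiority t-test (noncentral t), one-sided α 0.05: power is 0.893 at 15 per arm and 0.910 at 16, so n = 16.
- Dropout: 16/0.75 = 21.3, rounded up to 22 per arm, 44 in total.

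The stated 44 is reproduced, at one-sided 0.05. At one-sided 0.025, which a two-sided 0.05 implies, the same method gives 20 evaluable, 27 per arm and 54 in total. Either way the calculation uses only MMD inputs and says nothing about VAS or MSQOL.

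**2. Hypothesis, margin and test side by side.**

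| Outcome | Non-inferiority hypothesised | Margin | Test in section 6 |
|---|---|---|---|
| Attack frequency (MMD) | Sections 1 and 8 | 1 day | Two-sided difference |
| Pain intensity (VAS) | Sections 1 and 8 | None | Two-sided difference |
| Quality of life (MSQOL) | Section 1 only | None | Two-sided difference |

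The MMD row shows that section 6 does not apply the 1-day margin to MMD either. The fix has to cover that, or no stated non-inferiority test remains.

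**3. What p>0.05 would mean on VAS or MSQOL.** The document gives no SD, expected difference or important difference for these scales, so the deficits below are assumptions in SD units.

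For a two-sample t-test at two-sided 0.05 with n per arm, the degrees of freedom are 2n − 2 and the noncentrality is d·√(n/2). For d = 0.5:

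- n = 22: noncentrality 0.5 × √11 = 1.658, critical t 2.018, power 0.367. Chance of p>0.05: 0.633.
- n = 16: noncentrality 0.5 × √8 = 1.414, critical t 2.042, power 0.278. Chance of p>0.05: 0.722.

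The value 16 is the evaluable number behind the plan's own 22. Since 22 × 0.75 = 16.5, 17 is equally defensible and gives 0.707.

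Range over the assumed deficit:

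| True deficit | p>0.05, 22 per arm | p>0.05, 16 per arm |
|---|---|---|
| 0.3 SD | 84% | 87% |
| 0.5 SD | 63% | 72% |
| 0.8 SD | 26% | 41% |

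**4. Precision.** The 95% CI half-width in SD units is t × √(2/n):

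- n = 22: 2.018 × √(2/22) = 0.61.
- n = 16: 2.042 × √(2/16) = 0.72.

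An observed difference of zero would therefore still be compatible with a deficit of 0.61 to 0.72 SD.

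**5. Could a margin be added instead?** Take an illustrative margin of 0.5 SD, a true difference of zero, one-sided 0.025 and 90% power. Then n = 2 × (1.960 + 1.282)²/0.5² = 84.1, so 85 evaluable per arm. With 25% dropout, 85/0.75 = 113.3, so 114 per arm and 228 in total. At 80% power it is 63 evaluable, 84 per arm and 168 in total. The trial has 44.

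**The case against.** **A reader might infer that the plan will report p>0.05 as non-inferior, with a 63–72% error rate.** The document does not support that. Sections 1 and 8 state a hypothesis, not a claim, and no section says a non-significant VAS or MSQOL result will be read as non-inferiority. The percentages are the chance of a non-significant result under an assumed 0.5-SD deficit. They become error rates only if someone adds that reading rule.

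**A non-significant result is not the only route.** A significant FSN advantage would establish non-inferiority without a margin, and section 2.4 assumes a sizeable FSN advantage on MMD. This is correct, and the point is limited accordingly. No comparable assumption is given for VAS or MSQOL.

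**Large losses would usually be seen.** Also true: the t-test passes 50% power at about 0.61 SD with 22 per arm and about 0.72 SD with 16. The weakness concerns small to moderate deficits.

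**These are secondary outcomes in an exploratory trial, and margins for them could sit in a fuller protocol or SAP.** Sizing only the primary outcome is ordinary design, and the missing sizing is not the complaint. The article, however, is not silent here. It puts pain and quality of life into the trial's hypothesis and fixes a test for them, and the two do not match as written. The exploratory label lowers the stakes but does not turn a difference test into a non-inferiority test.

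**This is the MMD margin problem again.** In part: one sentence in section 6 covers all four measures. The MMD gap could be closed by using the margin already stated, whereas VAS and MSQOL have no margin to use.

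**Conclusion.** The point holds as a mismatch between the stated hypothesis and the stated analysis. Two of the three domains in the section 1 hypothesis have no margin, and their planned tests can support non-inferiority only through significant superiority of FSN. The hypothesis in sections 1 and 8 also differs in scope, since section 8 omits quality of life.

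The mismatch itself needs no numerical assumption: without a margin, p>0.05 rules out no particular deficit. Its illustrated size does rest on assumptions, namely a 0.5-SD deficit, a t-test and 16 to 22 evaluable per arm. It should be worth correcting before results are reported, but it concerns secondary outcomes and does not undermine the trial's conduct.

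**What to change.** - **Sections 1 and 8:** limit the non-inferiority hypothesis to MMD, in the same words in both places.
- **Section 6:** compare the confidence limit for the between-arm difference in MMD change with the 1-day margin, and state the confidence level. Without this step, the narrowed hypothesis would still have no matching test.
- **Section 6, VAS and MSQOL:** report between-arm differences with 95% confidence intervals, for MSQOL by dimension as section 4.2 scores it. State that p>0.05 on these measures will not be described as non-inferior or comparable.

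The alternative is to justify margins for VAS and MSQOL in advance, but step 5 of the working suggests that 44 participants would be too few for a moderate margin if the arms are truly equal.

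The cost is wording in three sections, with no extra participants, visits or data. The downside is a narrower claim: the trial could still describe pain and quality-of-life results, but not call them non-inferior on a non-significant test.

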## Methods and analysis

2

### Study design

2.1

This randomized controlled clinical trial will take place at Guangdong Provincial Hospital of Traditional Chinese Medicine between April 2025 and April 2026, following the Declaration of Helsinki guidelines. The hospital’s Ethics Committee approved the study (Approval No.: YF2025-127), which has been registered on a clinical trial platform (NCT07068815).

### Study setting

2.2

Participants are recruited from the acupuncture outpatient clinic and neurology outpatient clinic of Guangdong Provincial Hospital of Traditional Chinese Medicine. Eligible participants who provide consent are randomly assigned in a 1:1 ratio to receive either FSN treatment (*n* = 22) or pharmacological treatment (*n* = 22) for 4 weeks. Outcome measures are assessed for all participants at baseline, on day 28 after the initiation of intervention, and on days 28, 56, 84, 112, 140 and 168 after treatment completion. Additionally, NIRS measurements are performed for participants in the FSN group during the 1st, 3rd, 5th, and 7th treatment sessions within the therapeutic cycle.

### Participants

2.3

#### Inclusion criteria

2.3.1

Meeting the diagnostic criteria for migraine without aura (MwoA) according to the International Classification of Headache Disorders, 3rd edition (ICHD-3) (1);Aged 18–65 years;A history of migraine for at least 1 year;At least 2 migraine attacks per month (meet the diagnostic criteria for migraine without aura (criteria B–D) as defined by ICHD-3);No prophylactic medications or other treatments for migraine within the past month;Visual Analog Scale (VAS) score >3;Voluntarily provided written informed consent.

#### Exclusion criteria

2.3.2

Diagnosed with other primary headaches such as neuropathic headache, cluster headache, or tension-type headache;Comorbid secondary headaches or other neurological disorders (e.g., headache due to anxiety, depression, Parkinson’s disease, or intracranial lesions);Uncontrolled or undiagnosed systemic diseases that may interfere with the study, including severe hepatic, renal, cardiovascular, or cerebrovascular diseases; poorly controlled or untreated hypertension (systolic blood pressure exceeding 160 mmHg and/or diastolic blood pressure above 100 mmHg); poorly controlled or untreated diabetes mellitus; malnutrition; hyperthyroidism; or hepatic insufficiency;Comorbid uncontrolled psychiatric disorders;Presence of cervical spine disorders that may affect the assessment of neck and shoulder muscle function.Pregnancy, lactation, or women in the preparation, menstrual, or menopausal phase;Use of prophylactic medications or other treatments for migraine within the past month;History of allergy to the trial medications or contraindications to flunarizine hydrochloride or ibuprofen;Kin lesions at the FSN operation site;Occupations involving driving, working at heights, or other high-risk activities;Refusal to undergo FSN therapy or oral flunarizine hydrochloride.

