### Randomization and blinding

2.5

All eligible participants who provide informed consent are randomized in a 1:1 ratio to either the FSN group (*n* = 22) or the drug group (*n* = 22). Randomization is performed using a random number table with allocation concealment. The randomization sequence (seed 12345) is generated by methodology personnel not involved in treatment or evaluation using SAS 9.4 software, with a total of 44 random numbers selected. Forty-four allocation cards are prepared, each labeled with a sequential number and a corresponding random number. The cards are sealed in opaque envelopes marked with matching sequential numbers. The envelopes are kept by the statistician. Upon enrollment, the methodologist open the envelope corresponding to the participant’s sequential number and assign the participant to a group based on the random number.

Participant recruitment, intervention administration, outcome assessment, and statistical analysis are conducted independently by different researchers. Due to the nature of acupuncture, neither participants nor practitioners are blinded, but they are instructed not to disclose group allocation during follow-up assessments. To minimize measurement and subjective biases, a unified operational manual is developed to standardize all outcome assessment procedures. Outcome assessors and data collectors are blinded to group allocation and underwent a two-day training program, during which they are instructed not to communicate with participants regarding the intervention. Participants are also directed not to disclose their treatment assignments to the assessors and instructed to record symptoms based on actual experiences, avoiding the influence of treatment expectations. Data analysis is performed by blinded statisticians.

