### FSN therapy

3.1

Participants are seated while the practitioner identify affected muscles (sternocleidomastoid, scalene, splenius capitis, and upper trapezius) via sliding palpation. The palpation reveal tissue tension, rigidity, firmness, and a smooth, resilient texture, accompanied by cord-like changes. The affected muscle tissues may exhibit localized soreness and discomfort. After disinfection, a disposable FSN needle (diameter 0.60 mm, length 50 mm; Nanjing Paifu Medical Technology Co., Ltd., Jiangsu, China) is inserted parallelly to the subcutaneous loose connective tissue surrounding the affected muscle. Once fully inserted, the soft tube stand is secured in the slot. The operator then perform alternating sweeping motions using the index and ring fingers with an angle of 60°at a frequency of 100 sweeps per minute. This is accompanied by reperfusion activities—resistance-based contraction and relaxation of the affected muscles, performed collaboratively by the practitioner and participant. After 20 sweeping dispersions, a 10-s reperfusion activity is performed, with this procedure repeated 3 times for each affected muscle. Reperfusion methods for specific muscles are as follows:

Sternocleidomastoid: seated, the participant turn the head toward the unaffected side while the practitioner apply resistance to the affected side, prompting the participant to attempt turning toward the affected side.Scalene: seated, the participant tilted the head slightly toward the affected side while the practitioner resist, prompting the participant to attempt further tilting.Splenius Capitis: seated, the participant extend the head maximally (until the line between the ear apex and earlobe was horizontal) while the practitioner resist at the occiput, prompting the participant to attempt further extension.Upper Trapezius: seated, the participant maximally elevate the affected shoulder while the practitioner resist, prompting the participant to attempt further elevation.

The FSN group receive treatment twice weekly for 4 weeks.

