## Safety assessment

5

The primary clinical adverse reactions associated with Fu’s acupuncture needling are subcutaneous hemorrhage and needling syncope. Before the procedure, the operator should avoid needling in areas with dense vascularization. Upon completion of each Fu’s acupuncture session, prolonged pressure should be applied to the needle insertion site and along the needle track to prevent subcutaneous hematoma. Subcutaneous hematomas are graded according to the CTCAE criteria as follows: Grade 1 (Mild): Small hematoma with a diameter <2 cm; managed with local compression or observation. Grade 2 (Moderate): Hematoma measuring 2–5 cm; managed with compression, heat therapy, and temporary discontinuation of treatment if necessary. Grade 3 (Severe): Hematoma >5 cm with persistent bleeding; treatment is discontinued, and the patient is referred for clinical management.

In cases of needling syncope, the needles should be immediately removed. The participant should be placed in a supine position with legs elevated, and vital signs should be monitored. Symptomatic management, such as oxygen administration and hydration, should be provided as needed. Severe cases require prompt medical attention.

Flunarizine’s frequent adverse events are sedation, weight gain and extrapyramidal reactions (31). Body weight is measured every 2 weeks (on days 1, 14, and 28) to quantify weight increase (a change of ≥5% from baseline is considered clinically significant). Extrapyramidal symptoms (EPS), including tremor, akathisia, dystonia, and rigidity, are assessed using the Rating Scale for Extrapyramidal Side Effects (RSESE). Evaluations are conducted at baseline, Week 2, Week 4, and during follow-up by trained neurologists.

Criteria for drug discontinuation included persistent sedation (lasting ≥3 days and interfering with daily activities), moderate to severe EPS (CTCAE grade ≥2), or weight gain of ≥7% accompanied by the patient’s request to withdraw. All events are recorded in patient diaries and reviewed weekly by assessors.

All serious adverse events (SAEs) must be reported to the Ethics Committee within 24 h.

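### The exclusion criteria screen for contraindications to flunarizine and ibuprofen but not to FSN, so a patient on blood-thinning treatment for a controlled condition is not clearly excluded from needling

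*Protocol article*

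**What the plan says.** Exclusion criteria (2.3.2) prints 11 items. One is a general contraindication clause, and it covers the study drug and the rescue analgesic: "History of allergy to the trial medications or contraindications to flunarizine hydrochloride or ibuprofen". FSN is named in two items. One concerns lesions at the operation site (printed as 'Kin', evidently 'Skin'). The other is "Refusal to undergo FSN therapy or oral flunarizine hydrochloride". A further item covers "Uncontrolled or undiagnosed systemic diseases that may interfere with the study" and gives examples.

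Randomization and blinding (2.5) states that "All eligible participants who provide informed consent are randomized in a 1:1 ratio to either the FSN group" or the drug group, so eligibility must establish suitability for either arm. FSN therapy (3.1) describes needling of a seated patient twice a week for 4 weeks, which is 2 × 4 = 8 sessions.

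Safety assessment (5) says that the primary reactions associated with "acupuncture needling are subcutaneous hemorrhage and needling syncope". It then gives operator precautions, a three-grade hematoma scheme, and an acute response to syncope.

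**The concern.** When every eligible patient may receive either treatment, the criteria should remove those for whom either treatment is unsuitable. The printed list does this in general terms for flunarizine and ibuprofen. For the needle it does so only where the skin is damaged or the patient declines. The protocol itself names two primary reactions to FSN, and no item is directed at patients who may be prone to them.

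What is at stake is the safety of a few participants. Under the rule as printed, a willing patient with a bleeding tendency caused by medication could be enrolled and allocated to repeated subcutaneous needling. The matter bears on who is enrolled, not on the sample size or the analysis.

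**Working it through.** No arithmetic bears on this point. The check is to read each eligibility item that might protect an FSN patient against the reactions named in section 5.

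1. **Drug contraindication clause (2.3.2).** It covers flunarizine and ibuprofen. A clinician might treat some bleeding-prone patients as unsuitable for ibuprofen, so the clause may remove some of them incidentally. The document does not say so, and the clause does not address fainting on needling.

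2. **Systemic-disease item (2.3.2).** It opens with "Uncontrolled or undiagnosed systemic diseases that may interfere with the study". Its examples include severe hepatic, renal, cardiovascular and cerebrovascular disease, malnutrition and hepatic insufficiency. Some patients with a bleeding tendency would be caught here. The examples name no coagulation disorder and no anticoagulant or antiplatelet use. A patient whose condition is diagnosed and controlled, and who takes such a drug, falls outside the opening words.

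3. **Cervical spine item (2.3.2).** The stated reason is that such disorders may affect the assessment of muscle function. It is not a needling-safety criterion.

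4. **Site lesions (2.3.2).** This concerns the local skin, not a general tendency to bleed or faint.

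5. **Refusal (2.3.2).** It does not reach a patient who is willing to be needled.

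6. **Inclusion criteria (2.3.1).** Diagnosis, age, migraine history, attack frequency, no recent treatment for migraine, VAS score and consent: none addresses either reaction.

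7. **Safety assessment (5).** For bleeding, the operator is to avoid highly vascular areas and apply prolonged pressure afterwards. Hematomas are graded by size: treatment may be paused at Grade 2, and at Grade 3 the rule is "Hematoma >5 cm with persistent bleeding; treatment is discontinued, and the patient is referred for clinical management". For syncope, the needles come out and acute care follows. These measures act during or after needling; they do not select participants.

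Side by side: there is one general contraindication clause for the drugs and none for FSN. Of the 11 exclusion items, 2 name FSN, and neither concerns a tendency to bleed or faint. The clearest uncovered case is the patient on blood-thinning treatment for a controlled condition.

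**The case against.** The strongest reply is that this is an absence, not an error. Nothing printed is false or contradictory, and a journal article condenses a fuller protocol that may contain needling contraindications. That limits confidence. It does not dispose of the point, because 2.3.2 is a detailed list, down to blood-pressure limits and occupations, and it includes a contraindication clause written for the drugs only. The comment is on how that printed clause is drawn.

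A second reply is that the document identifies no group at higher risk and calls nothing a contraindication to FSN. That is correct. The link between a bleeding tendency and subcutaneous hemorrhage is a clinical assumption, though a modest one. The same link for an earlier needling faint has less support, which is why the fix leaves it to judgement.

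A third reply is that existing text already does much of the work. This stands in part: the ibuprofen and systemic-disease items, the recording of medical and medication history under Intervention (3), and the section 5 precautions all reduce the risk. Recording a history does not, however, make a patient ineligible.

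Some stronger readings are tempting but unsupported. A reader might infer that the protocol ignores FSN safety; section 5 shows otherwise. A reader might infer a serious bleeding hazard; the document speaks of subcutaneous hemorrhage, graded by hematoma diameter. A reader might try to size the risk from the planned dose of needling; nothing in the document links dose to either reaction. A reader might also object that section 5 prints no rule on further sessions after a syncope. That concerns management after the event, and an eligibility criterion would not settle it.

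**Conclusion.** The point holds as a minor patient-safety improvement. The exclusion list screens for contraindications to the drugs but, for FSN, only for site lesions and refusal. As a result, a willing patient on anticoagulant or antiplatelet treatment for a controlled condition is not clearly excluded from an intervention whose named primary reactions include subcutaneous hemorrhage. The case for screening on previous needling syncope is weaker.

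The number of patients concerned is unknown and probably very small; the document gives no prevalence and none is assumed. The conclusion rests on two assumptions: that a bleeding tendency predisposes to the named reaction, and that no such clause stands in a fuller protocol that is not shown. A reader might infer that the gap biases the comparison of the arms. The document gives no basis for that, and no effect on the efficacy result or the adverse-event comparison is claimed.

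**What to change.** Extend the existing clause in 2.3.2 so that it reads, in substance: *contraindications to flunarizine hydrochloride, ibuprofen or FSN (bleeding tendency, including from anticoagulant or antiplatelet medication; and, at the investigator's judgement, previous syncope on needling)*.

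Check it from the medical and medication history before allocation. Table 1 places eligibility and allocation both on Day 0, and section 3 promises the history only before formal intervention, so the order should be made explicit.

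The cost is a line of amendment and possibly a few extra screen failures. No new procedure is needed, because the history is already collected and the existing drug-contraindication and prior-treatment criteria already depend on it.
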